### Data collection and outcome measurements

#### Implementation study

Data will be collected on implementation through self-reports from group leaders/teachers on the implementation of the method and how they experienced it. These self-reports will be completed together with the leaders/teachers implementing the method after 6 months.

Measures of the extent to which the children have been exposed to the method and how well the leaders implemented the method will be taken. Barriers and success factors in implementation will also be assessed by interviews with a subgroup of deliverers (*n* = 10). Observations will be performed using implementation checklists twice a year as the method is conducted to study the implementation of the method. The aspects of the implementation of the program that will be the focus of the evaluation are: dose or exposure, program fidelity, customization, quality of the implementation of the program (quality of delivery), and how participants react to the program and its implementation. Implementation is a key aspect of prevention and health promotion because it affects the results achieved by the intervention [50, 51].

#### Effect study

To measure the effects of the program, we will use child reports (self-reports) and adult reports. Data from the children will be collected to enable analysis of program effects and effects on children’s resilience, health and well-being. These factors have a strong connection with the harmful use of alcohol/drugs, and the outcome measurements can also be seen as intermediate effects in relation to longer-term outcomes (which must be measured when participants are several years older) and that concern the use of ANDT. We will investigate how the method works for different groups based on age, gender, place of residence, and problem levels. During the planning phase, a balance has been made between obtaining data that is age-appropriate for the children on the one hand, and the ability of researchers to perform more sophisticated analyses on the other.

#### Self-reports from the children

All measures have been translated into Swedish in previous research projects, and the psychometric tests have been shown to work well in the age groups we are evaluating. The instruments that we will use are the following:Child and Youth Resilience Measure (CYRM) [52]. In order to make the evaluation as change-sensitive as possible, we will use the variant with a 5-point Likert scale, instead of the 3-point.How I feel (HIF) [53] is used for older children, and further development of the instrument for younger ages is underway in our EU Comenius Project European Assessment Protocol for Children’s SEL skills [How one feels (HOF)].Health, psychiatric symptoms, somatic symptoms and health behaviors from HBSC (Health Behaviour of School-aged Children) [54, 55],Mastery [56]Demography (gender, age, housing situation, family structure).

#### Reports from adults

At least one adult per child will fill in instruments about the child’s behavior. For the school group, this will be the child’s teacher. For the social services group, it is primarily a parent, or secondarily a social worker, who will respond. For the Junis groups, leaders are assessing the behavior of the child. The adults will fill in two instruments. Both instruments have previously been translated into Swedish, and both have been shown to have good psychometric properties.Child and Youth Resilience Measure - Person Most Knowledgeable (CYRM) [33, 57]. In order to make the evaluation as change-sensitive as possible, we will use the variant with a 5-point Likert scale, instead of the 3-point. This is exactly the same measure that the children themselves may fill in.Strengths and difficulties questionnaire (SDQ) [58, 59]. SDQ is an international and widely used instrument, and is also a widely used measure in Sweden.

The school classes and groups who will fill in surveys will receive as small economic token in appropriate forms from the research project.

### Data management and analysis

All collected material from surveys, observations and interviews will be encoded before analysis. The code key, with the researcher’s name and code number, will be stored separately in fireproof locked cabinets, which only research director [name] has access to. All collected material will be stored for at least 10 years in other fireproof archives, as required by law. All primary data will be stored at Göteborg University. Because the project has a longitudinal design, the research participants are not anonymous. However, it is of the utmost importance that the principle of confidentiality is followed. The names, addresses or the like of the children, parents or co-workers will not be read-in without being treated confidentially and only for this project. The results are only reported at group level, which means that individuals cannot be identified.

The research group has monthly meetings together with the implementing organization in order to facilitate the smooth running of the intervention study. In order to answer the five research questions, both quantitative and qualitative analyses will be applied in this intervention study, which uses a mixed methods research approach. The quantitative data will be managed using SPSS as a tool for analysis. In the randomized trial, we will use latent change models to examine the changes in child outcomes over time. To obtain unbiased estimates despite attrition, we will employ intention-to-treat analysis. Cohen’s *d* effect sizes were computed to estimate the effects of the programs compared with the wait-list condition while taking the initial level of each outcome measure into account. The social services and the NGO groups will be compared with controls matched from the waiting list controls. Mediating and moderating factors will be analyzed with regard to the primary outcomes.

The interviews will be transcribed and analyzed by qualitative content analysis. All sources of data will be used in the implementation study, where the inferences will be drawn using mixed-methods procedures.

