**Table 1 Tab1:**
[figure not shown]
Schedule of enrolment, interventions, and assessments

The controlled study has three different arms. In the case of schools, we cluster-randomized participants to one of two conditions: (A) intervention schools or (B) waiting list or control schools. Randomization has been done at school level. Thereafter, the baseline measurements were performed in both conditions, and, after that, the intervention group began its activities, and measurements were taken as described above (Table 1). One year after the baseline measurement intervention group (A), the waiting list group began its program. Measurements are finally to be made a year later.

In the case of Junis’s groups, it was not feasible to do a cluster randomization at the managerial level as the involvement of local chapters was more difficult to achieve. The groups will be led by regular Junis volunteers.

As for the social services group, we will have the same arrangement, but no waiting-list control condition. Here, a new round of groups is planned for the second year. On the other hand, we will have a follow-up measurement of the first wave’s intervention groups in year 3 for both the Junis and the social services groups. The groups will be run by social workers.

However, it will be possible to compare developments in these two study arms with the data collected in the control schools.

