### Participants and recruitment

A calculation of statistical power has been made for the interventions. For the universal intervention, there is an effect size of d = 0.3 and a power of 0.8, and the corresponding statistics are expected to test a group size of 176 in each group. The recruitment of schools for the evaluation of RESCUR has been completed. These schools have been recruited from different parts of Sweden, and in both urban and rural areas. There are 8 intervention schools in five municipalities, including 10 classes in school year 1, and 8 classes in school year 4. The intervention group includes 394 children. There are 9 school in the waiting list control schools in six municipalities, including 10 classes in school year 1, and 9 classes in school year 4. The waiting list controls include 401 children. The number of classes in which RESCUR is carried out in the municipalities is larger than necessary to carry out the project based on an evaluation or “power perspective”. Oversampling, however, is a common and good strategy to deal with any delays, etc. from the project, and thus to reduce threats to the implementation of the project. Participants are randomized to the intervention and waiting list/ control groups based on residence and school. The planned survey is regarded as having adequate statistical strength.

The project group has trained 23 teachers in the intervention schools. In March 2018, 20 teachers in the waiting list control schools will be trained in the RESCUR intervention.

A power analysis for the interventions in social services and the NGO has been performed. For the selective groups, an effect size of d = 0.5 and power of 0.8 is calculated, which results in a double-sided statistical testing of group differences (alpha = 0.05), and a group size of 64 children in each of the two groups. The planned size allows for a certain amount of dropout in the study.

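### Seventeen schools were randomised, but the stated effect analysis has no school level and the stated sample size treats children as independent

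*Protocol article*

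**What the plan says.** **Unit of allocation.** The Design section, in the text after Table 1, says of the schools that "we cluster-randomized participants to one of two conditions", and then that "Randomization has been done at school level". The section Participants and recruitment describes it differently: "Participants are randomized to the intervention and waiting list/ control groups based on residence and school".

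**Numbers.** Participants and recruitment reports: "There are 8 intervention schools in five municipalities"; "There are 9 school in the waiting list control schools in six municipalities"; "The intervention group includes 394 children"; "The waiting list controls include 401 children".

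**Sample size.** The same section gives 176 per group for the school comparison, from d = 0.3 and power 0.8. It calls the number of classes more than the evaluation needs and the statistical strength adequate.

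**Analysis.** Data management and analysis states: "In the randomized trial, we will use latent change models to examine the changes in child outcomes over time". It adds intention-to-treat, Cohen's d against the wait-list condition allowing for the initial level of each outcome, matched controls for the two non-randomised arms, analyses of mediators and moderators, and SPSS for the quantitative data. It does not mention schools or classes as levels, clustering, an ICC or cluster-robust standard errors.

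**The concern.** In a school-randomised trial, children in one school share staff, neighbourhood and delivery of the programme, so their outcomes are correlated. The information on the arm effect comes mainly from differences between the 17 schools and much less from the count of 795 children. An analysis that takes the children as independent understates the standard error, narrows the interval around Cohen's d, and can present ordinary between-school variation as a programme effect.

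Two features of the article make this more than a matter of brevity. The article does name its effect model and effect-size measure, and neither reflects the allocation it describes. And the one piece of planning that can be checked, the sample size, leaves clustering out. This is the only randomised comparison in the project, so its error rate matters most.

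**Working it through.** **Inputs from the article.** 8 + 9 = 17 schools; 394 + 401 = 795 children; d = 0.3; power 0.8; 176 per group. Two-sided alpha of 0.05 is stated for the selective groups only and is assumed here for the schools too. No ICC is given, so values from 0.005 to 0.10 are assumed. The relevant ICC is that of the change score or baseline-adjusted outcome.

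**Step 1: reproduce the plan's figure.** With the normal approximation, n = 2 × (1.960 + 0.842)² / 0.3² = 174.4, so 175 per group. The t-test version gives 175.4, so 176, which matches. A one-sided test gives 138, which does not match. The figure of 64 per group for d = 0.5 is reproduced in the same way (63.8 by t-test). Both figures correspond to a design effect of 1.

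**Step 2: size of the clusters.** m = 795 / 17 = 46.8 children per school (49.3 in the intervention arm, 44.6 in the control arm).

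**Step 3: consequence if schools are left out of the model.**

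- Design effect: DE = 1 + (m − 1) × ICC = 1 + 45.8 × ICC
- Ratio of the reported to the true standard error: 1/√DE
- Type I error of a nominal 5% test: 2 × [1 − Φ(1.96/√DE)]
- Effective children per arm: 397.5 / DE, where 397.5 = 795 / 2

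| Assumed ICC | DE | SE ratio | Type I error | Simulated | Effective n per arm |
|---|---|---|---|---|---|
| 0 | 1.00 | 1.00 | 5.0% | 5.0% | 398 |
| 0.005 | 1.23 | 0.90 | 7.7% | not run | 323 |
| 0.01 | 1.46 | 0.83 | 10.5% | 10.1% | 273 |
| 0.02 | 1.92 | 0.72 | 15.7% | 16.5% | 208 |
| 0.05 | 3.29 | 0.55 | 28.0% | 28.2% | 121 |
| 0.10 | 5.58 | 0.42 | 40.7% | 40.5% | 71 |

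The simulation used 8 and 9 schools of near-equal size (44 to 50 children, totalling 394 and 401) and 6,000 runs per ICC. The article does not give the individual school sizes.

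An SE ratio of 0.90 to 0.42 means that correct intervals would be about 1.1 to 2.4 times as wide as the reported ones (√1.23 = 1.11; √5.58 = 2.36).

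**Step 4: the surplus over 176.** Effective n falls below 176 per arm once DE exceeds 397.5 / 176 = 2.26, that is, once the ICC exceeds 1.26 / 45.8 = 0.0275. Above that value the surplus claimed in Participants and recruitment no longer exists.

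**Step 5: does a valid analysis exist with these data?** In the same simulation, a t-test on the 17 school means (8 + 9 − 2 = 15 degrees of freedom) rejected in 4.7% to 5.2% of runs at every ICC tried. Its calculated power at d = 0.3 is 94.5%, 90.5%, 81.4%, 58.7% and 38.7% for ICC 0.005, 0.01, 0.02, 0.05 and 0.10.

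**The case against.** A reader might infer that the plan specifies a single-level analysis and that its standard errors will therefore be too small. The documents do not support that. The phrase about child outcomes names what is measured, not the level of the model. A latent change model can carry a school level or cluster-robust standard errors. The article condenses a fuller plan that is not shown, and random effects and degrees of freedom are often left to such a plan. The authors also openly describe the allocation as clustered.

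The sample size does not close the gap. It shows that clustering was left out of the planning calculation, which is a fault in itself, but it is only circumstantial evidence about the analysis. Nor does the mention of SPSS show anything, since SPSS can fit mixed models.

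The size is also conditional. No ICC is given, and adjustment for baseline may make the relevant one small. At 0.005 the error rate is 7.7%, a modest excess over 5%.

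All of this stands, and it limits the point to a conditional one. It does not remove the point: the article states the model, the effect size and the sample size, and none of the three reflects the school allocation it reports. Nothing in the text directs an analyst to use the school as the cluster.

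**Conclusion.** The point holds in conditional form. The article reports 17 randomised schools, states an effect analysis with no school level, and states a sample size that assumes independent children. If the analysis were carried out as written, without a school level, a nominal 5% test would reject a true null in about 8% to 41% of trials, for an assumed ICC of 0.005 to 0.10 and about 46.8 children per school. These figures rest on the assumed ICCs, a two-sided 5% test for the school comparison and near-equal school sizes.

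The documents do not establish that the models are single-level. They do establish that the stated planning takes no account of the randomised unit, and that the unit itself is described in two ways. Both should be settled before the randomised comparison is analysed.

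**What to change.** **In Data management and analysis**, state that the randomised comparison accounts for school as the randomised cluster. Any of these would do:

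- a two-level latent change model;
- a mixed model with a random effect for school;
- an analysis of baseline-adjusted school means.

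Whichever is chosen, name small-sample inference suited to 17 clusters (about 15 degrees of freedom), and report Cohen's d with a cluster-adjusted confidence interval. Further covariates, a class effect within school and the particular degrees-of-freedom method are for the trial team to choose.

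**In Design and in Participants and recruitment**, make the two descriptions of the randomised unit agree (school, or residence and school), and use that unit as the cluster level.

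**For the sample size**, say that 176 per group carries no allowance for clustering. Recruitment of schools is complete, so the useful step is to restate the power of the 8 versus 9 schools over a range of ICCs, as in Step 5.

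**Cost.** A few sentences and slightly more analysis work, with no new data. Confidence intervals become wider, and at the higher ICCs power at d = 0.3 falls below the planned 0.8.

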### Research design and methodology

The project has been divided into three phases. The first phase involved planning and conducting a preliminary study, including the application to the research ethics committee (first year). We started the project, formed a project team and appointed a project manager, worked on the manuals to make them more user-friendly, gave information about and marketed the project among organizations and policy-makers, recruited participants for the evaluation, finalized the project and research plan, including all measuring instruments. The Ethical Review Board approved the research project (EPN dnr 2016/460).

The project is based on close collaboration between Junis and the research group, with a clear division of work and responsibility. The purpose of Junis’s activities is to provide health promotion for children aged 7–15 years in an encouraging environment where the child’s self-esteem and self-confidence grow together with secure and safe adults. The organization will be responsible for planning and implementing the program in all groups. The research group is responsible for the scientific study of implementation and effects of the program for the participants in groups and school classes who are part of the intervention and control groups. The research consists in a randomized, controlled, longitudinal survey of the RESCUR program. This means taking baseline measurements before the intervention begins, and follow-ups at 6 months, 1 year, and then 2 years.

The second phase involves implementing the program “I want, I can, I dare” (RESCUR) in Junis’s group activities, in groups throughout social services and in school classes in different municipalities and across the country (i.e., in different residential areas). The third phase involves analysis and reporting on the project’s implementation and its effects.

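### The protocol credits intention-to-treat analysis with removing attrition bias, a property it does not have; the missing-data method and its assumption should be named instead

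*Protocol article*

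**What the plan says.** The only statement on attrition and bias is in Data management and analysis: "To obtain unbiased estimates despite attrition, we will employ intention-to-treat analysis". The sentence before it names the model: "In the randomized trial, we will use latent change models to examine the changes in child outcomes over time". The sentence after it says that Cohen's d will take the initial level of each outcome into account. The software sentence is "The quantitative data will be managed using SPSS as a tool for analysis". None of these names an estimator or an assumption about why data are missing, and none connects the latent change model to dropout.

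Research design and methodology sets "follow-ups at 6 months, 1 year, and then 2 years" after baseline. According to the Design section, adult reports are collected only at baseline and 1 year, and the waiting-list schools start the programme 1 year after baseline.

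Participants and recruitment deals with loss only through numbers. More classes were recruited than the power calculation needed, and the size planned for the social services and NGO groups is said to leave room for some dropout.

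**The concern.** The sentence names a remedy for attrition and states what that remedy achieves. Intention-to-treat protects the comparison from reclassifying or excluding children according to how much of the programme they received. It is silent on children whose outcome is unknown. A child can be kept in the randomised arm and still contribute no follow-up score. What happens next depends on the estimation method and on the reason for the missing score.

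This is something the article asserts, not a detail it leaves out. An analysis plan that is not shown could add a missing-data method, but it could not make the sentence true as it stands.

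The main randomised comparison is at stake. Children aged 7 to 12 are followed over three waves. One set of schools runs the programme while the other waits a year, so loss could plausibly differ between arms. At 6 months and 2 years only the child's self-report is collected, so no adult report from that wave is available to inform a missing score. A reader who accepts the sentence would take the estimate as protected when no stated feature of the analysis gives that protection.

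**Working it through.** **1. The plan's own figures.** For the schools, Participants and recruitment gives 176 per group, at d = 0.3 and 80% power. Alpha is not given there, so I take 0.05 two-sided, as in the calculation for the selective groups.

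- Normal approximation: n = 2(1.960 + 0.842)² / 0.3² = 175 after rounding up. The two-sample t-test gives 175.4, hence 176. Reproduced.
- Selective groups at d = 0.5: the normal approximation gives 63; the t-test gives 63.8, hence 64. Reproduced.

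No figure is in dispute. On the plan's own terms, which ignore clustering, the 394 and 401 recruited children exceed 176 per group even after losing 1 − 176/394 = 55% and 1 − 176/401 = 56%. That margin protects power. Extra children do not remove bias when loss is selective.

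**2. Does keeping the randomised arm remove the bias?** A large-sample simulation checks this. Its inputs are assumptions, because the article gives none of them:

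- 2,000,000 children, half per arm, with no clustering;
- baseline standard normal and baseline–outcome correlation 0.5;
- true effect 0.30 SD;
- about 20% dropout in each arm.

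Every child stays in the randomised arm, and only observed outcomes are used.

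| Why children are lost | Difference at follow-up | Difference in change | Baseline-adjusted |
|---|---|---|---|
| Completely at random | 0.30 | 0.30 | 0.30 |
| Low baseline, intervention arm only (random in control) | 0.39 | 0.21 | 0.30 |
| Low unseen outcome, intervention arm only (random in control) | 0.47 | 0.38 | 0.43 |

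The allocation rule is the same in every cell, yet estimates run from 0.21 to 0.47 around 0.30. Bias is absent when loss is completely random, or when it depends on baseline and baseline is modelled. Realised dropout was nearly equal between arms throughout (19% to 21%), so similar attrition rates would not be enough to show absence of bias.

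**3. An illustration of size.** Let *a* be the attrition in an arm and *g* the amount by which lost children are worse than retained ones, equal in both arms.

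- Mean of all = (1 − a) × observed mean + a × (observed mean − g) = observed mean − a·g.
- So the observed mean is too high by a·g, and the arm difference is off by (a₁ − a₂) × g.
- With g = 0.5 SD: (0.20 − 0.10) × 0.5 = 0.05 SD, and (0.30 − 0.10) × 0.5 = 0.10 SD.
- Against d = 0.3 these are one sixth and one third of the design effect.

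The direction follows whichever arm loses more children. The 0.5 SD must be the gap that remains after accounting for baseline, since the plan models change and adjusts effect sizes for the initial level. Any part of the gap already present at baseline would be reduced or removed by suitable modelling.

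**The case against.** The strongest defence is that the two sentences belong together. The latent change model, fitted by full-information maximum likelihood, uses children with partial records and is valid under missing-at-random. Intention-to-treat is also often used loosely to mean that everyone randomised stays in the analysis. On that reading the plan is sound and the sentence only badly phrased. The part that stands is that the named model could handle dropout. The claim itself does not stand: the estimator is not given, the protection is credited to intention-to-treat, and missing-at-random is a condition that the sentence omits.

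A reader might infer three stronger things that the document does not support:

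- **That children without a follow-up score will be discarded.** No complete-case rule is written anywhere.
- **That the plan has no means of dealing with dropout.** It names a model that may well do so; it does not say that it will.
- **That the missing detail on imputation, auxiliary variables or sensitivity analysis is itself a fault.** A condensed article commonly leaves this to the full protocol or analysis plan, which are not shown.

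It is also fair to say that the largest simulated bias comes from loss driven by the unseen outcome in one arm. Likelihood or imputation under missing-at-random would not cure that. This is a reason for a sensitivity analysis and for dropping the unconditional claim.

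**Conclusion.** The sentence is wrong as written, in a limited way. Intention-to-treat does not secure unbiased estimates when outcomes are missing, and the oversampling and dropout allowance do not do so either. The latent change model may, if it is fitted by a method that uses partial records and if missing-at-random holds; neither is stated.

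Bias could be material if loss differs between programme and waiting-list schools. It would be too strong to say that the result will be biased, or by how much. The article gives no attrition rate, no difference between arms and no gap between lost and retained children. The 0.05 and 0.10 SD figures rest entirely on the assumed rates and the assumed residual gap of 0.5 SD. Confidence is high on the narrow point about what intention-to-treat achieves, and low on any particular size.

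**What to change.** Replace the sentence with text that separates the two matters, for example:

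*All consenting children are analysed in the arm to which their school was randomised (intention-to-treat). Missing outcomes are handled by full-information maximum likelihood in the latent change model, or by multiple imputation, allowing for school clusters and using baseline and earlier waves, under the assumption that data are missing at random. A sensitivity analysis examines departures from that assumption.*

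Choose one of the two missing-data methods as the main one, and delete the unconditional claim of unbiasedness. Further detail can sit in the analysis plan.

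The cost is a short rewording, some extra analysis and a more modest claim. No new data or change to the conduct of the trial is needed.
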